### X-ray assessment

Marginal bone loss (MBL): immediately after placement of the final prosthesis, a periapical radiograph of each implant will be obtained as well as every year afterward. For standardization, a paralleling technique will be conducted using an intramural digital system (Digora Toto, Soredex, Tuusula, Finland). Kodak Dental Imaging 6.1 software (Carestream Health, Inc., Rochester, NY, USA) will be used for radiographic analysis. The crestal bone level will be measured as the vertical distance between 2 mm below the implant–abutment interface and the most crestal part of the alveolar bone [23, 24]. MBL will be measured mesially and distally for each implant. In each group, peri-implant MBL will be measured to the nearest millimeter.

A peri-implantitis lesion is defined as having PD of ≥ 5 mm with positive suppuration or BI of ≥ 1 and radiographic evidence of bone loss (> 2 mm) or according to consensus [25]. Peri-implant mucositis is defined as being positive for suppuration or BI of ≥ 1 with no radiographic evidence of bone loss. A healthy implant site is defined as a PD of ≤ 4 mm, BI = 0, and no radiographic evidence of bone loss.

The incidences of peri-implantitis and peri-implant mucositis will be determined at 1, 3, and 5 years after final restoration.

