### Sample size

The sample size has been calculated with NCSS-PASS software. At 5 years, peri-implant bone loss in metal-resin/metal-ceramic IFCDPs was 0.9 ± 0.4 mm and peri-implant bone loss in ceramic IFCDPs was 0.6 ± 0.1 mm [26]. In the proposed study, the criterion for significance is set at *α* = 0.05 (type I error) and *β* = 0.10 (type II error). The analysis is two-tailed. Assuming a dropout rate of 20%, in order to determine if there is a difference in the degree of bone loss between the two groups, 22 cases per group and 44 cases in total will be required. A previous study included 20 edentulous subjects who received two mandibular implants [10]. The abutments were either titanium or zirconium dioxide (non-submerged implant placement, within-subject comparison, left-right randomization). After 3 months, mean absolute counts of *Porphyromonas gingivalis* of the titanium vs. zirconia abutment were 1,000,000 ± 0 vs. 64,000 ± 36,770, respectively. However, the difference between groups was not evaluated in this study. Mean absolute counts (mean) for *Prevotella intermedia* of the titanium vs. zirconia abutment were 600,088 ± 952,117 vs. 3,600,089 ± 804,935, although the difference between the two groups was not evaluated. In this study, the criterion for significance will be set at *α* = 0.05 (type I error) and *β* = 0.10 (type II error). The analysis will be two-tailed. Assuming a dropout rate at 20%, in order to determine if there is a difference in the amounts of *P*. *gingivalis* and *P. intermedia* between the two groups, three patients per group and six patients in total will be required.

In summary, the total sample size will be 44 (22 per group).

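### Marginal bone loss is recorded to the nearest millimetre although the trial is sized on a 0.3 mm difference; the power lost ranges from small to large, depending on facts the protocol does not give

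*Protocol article*

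**What the plan says.** Under X-ray assessment, the protocol article takes a periapical radiograph of each implant at placement of the final prosthesis and yearly afterwards, with a digital system and analysis software. Crestal bone level is read as a vertical distance from a reference on the implant, mesially and distally. The section then fixes the unit: "In each group, peri-implant MBL will be measured to the nearest millimeter". No other section gives a finer one.

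Under Sample size, the planning values are "peri-implant bone loss in metal-resin/metal-ceramic IFCDPs was 0.9 ± 0.4 mm" and "peri-implant bone loss in ceramic IFCDPs was 0.6 ± 0.1 mm", with two-sided α = 0.05, β = 0.10 and 20% dropout, leading to "22 cases per group and 44 cases in total will be required". The bacterial calculation in the same section needs only three patients per group, so bone loss sets the size of the trial. Marginal bone resorption is among the listed primary outcomes. Under Statistical analysis, X-ray indices are compared by an independent t test, and a generalized estimating equation is planned for multiple implants in one patient.

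**The concern.** The two sections do not fit each other. The recording step is 1 / 0.3 = 3.3 times the difference the trial is meant to detect and 1 / 0.1 = 10 times the SD assumed for zirconia. A typical reading in either arm, 0.6 or 0.9 mm, would be written down as 1 mm.

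Rounding this coarse can do two things. If the loss itself is rounded, it can pull the arm means together. If bone levels are rounded and then subtracted, it adds noise. Either way information is discarded on the outcome that determines the sample size. The whole-millimetre unit is understandable for probing depth, which is read from a graded probe under Clinical assessment. Bone loss is measured in software on digital images, and the protocol gives no reason for whole millimetres there.

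**Working it through.** **Inputs from the protocol.** Means 0.9 and 0.6 mm; SDs 0.4 and 0.1 mm; two-sided α = 0.05; power 90%; 22 per group; dropout 20%; two sites per implant and 4–6 implants, so 8–12 sites per patient.

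**Assumptions, not in the protocol.** Normal values; cited SDs taken as patient-level; within-patient site SD varied from 0 to 0.5 mm; 10 sites per patient; for the bone-level reading, baseline levels uniform within a millimetre. Patient means are compared by Welch's t test, as a simple stand-in for the planned analysis.

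**The plan's own figure.** The pooled SD is √((0.4² + 0.1²)/2) = 0.2915. By the normal formula, n = 2 × (1.960 + 1.282)² × 0.2915² / 0.3² = 19.9, so 20 per group. Noncentral-t versions give 21 (pooled) or 22 (Welch). Dividing by 0.8 for dropout gives 25, 27 or 28. The stated 22 therefore matches the Welch figure before dropout and does not include the 20%. That is a separate matter. Here it only fixes the number left at the end: 22 × 0.8 = 17.6, taken as 18 per arm, with unrounded Welch power of about 83%.

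**Worst-case bound: loss is rounded and all sites in a patient are alike.**
- Share rounding to 0 mm (true value below 0.5): titanium z = (0.5 − 0.9)/0.4 = −1; zirconia z = (0.5 − 0.6)/0.1 = −1. Both are about 16%, so about 84% in each arm become 1 mm or more.
- Titanium values rounding to 2 mm: z = (1.5 − 0.9)/0.4 = 1.5, about 7%.
- Rounded means: 0.908 (SD 0.47) and 0.841 (SD 0.37). The difference falls from 0.30 to 0.067 mm.
- Power at 18 per arm: about 7%.

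**Sites vary within a patient.** Each site is rounded, then averaged over the patient's 10 sites (simulation, 18 per arm):

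| Within-patient site SD (mm) | Mean difference after rounding (mm) | Power unrounded | Power rounded | Loss (points) |
|---|---|---|---|---|
| 0 | 0.07 | 83% | 7% | 76 |
| 0.1 | 0.15 | 83% | 24% | 59 |
| 0.2 | 0.23 | 83% | 53% | 30 |
| 0.3 | 0.28 | 79% | 67% | 12 |
| 0.5 | 0.30 | 73% | 69% | 4 |

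Repeat runs agree to within about 2 points. Each row is compared with the unrounded power at the same site SD, because site variation lowers power even without rounding.

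**Two bone levels are each rounded, then subtracted.** The mean difference stays at 0.30 mm on average and only noise is added. At site SD 0, power falls from about 83% to about 75%. Over the range of site SDs the cost is about 6 to 9 points.

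**Recording to 0.1 mm.** Power equals the unrounded figure within simulation error in every setting, provided the reading itself is accurate to that unit.

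**The case against.** A reader might infer from the 0.067 mm difference and 7% power that the trial cannot detect its target effect. The protocol does not support that. The figure needs two conditions together: the loss itself is rounded, and all 8–12 sites in a patient have identical loss. The second is a boundary case. When sites differ, averaging rounded readings restores much or all of the mean difference.

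The X-ray section can also be read another way. What it defines as measured is a bone level on each radiograph. If levels are rounded and loss is their change, the mean difference survives and the cost is modest. Because the rounding sentence names bone loss and the definition describes a level, the text leaves this open.

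Nor should the rounding SD of one reading, √(1/12) = 0.29 mm, be set beside the pooled planning SD of 0.29 mm. With independent errors over 10 sites it becomes 0.29/√10 = 0.09 mm, or about 0.13 mm for a change of two rounded levels.

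The sentence may also be a slip, since the same unit is used for probing depth. And the protocol does not say whether the cited SDs are per patient or per implant.

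All of this limits the size of the problem. It does not remove it: the written rule is explicit, no finer unit appears elsewhere, and every setting examined loses power.

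**Conclusion.** The point holds as a mismatch between the recording unit and the planning values, with a conditional cost. At 18 per arm and 10 sites per patient, rounding the loss costs about 4 points of power at a site SD of 0.5 mm, 12 at 0.3 mm and 30 at 0.2 mm. The cost is larger still as sites become more alike, down to the bound of about 7% power. Rounding two levels and subtracting costs about 6 to 9 points. These figures rest on normality, patient-level SDs and a comparison of patient means. The protocol gives neither the within-patient site SD nor a clear statement of which quantity is rounded, so no single figure can be claimed. It is correct to say that whole-millimetre recording can hide the effect. It is not correct to say that it will.

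**What to change.** Replace the sentence under X-ray assessment with: 'MBL will be measured in the imaging software and recorded to at least 0.1 mm, and analysed without rounding to whole millimetres.' Leave probing depth at 1 mm, and leave the handling of multiple implants as the Statistical analysis section has it.

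The cost is negligible: the radiographs and software are the same and no extra patients are needed. The protocol states neither the resolution of the software nor the examiners' error on radiographs, so reading error at 0.1 mm should be reported alongside. Any readings already stored in whole millimetres can be measured again from the digital images.

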### Clinical assessment

Clinical examinations will be performed at baseline (immediately after prosthesis placement) and every 6 months after implantation of the final prosthesis.

The following parameters will be evaluated: PLI, bleeding index (BI), suppuration (0/1), and probing depth (PD). PLI, suppuration, and PD will be evaluated at four sites per implant (mesiobuccal, buccal, distobuccal, and lingual/palatal) [20]. The PD will be measured to the nearest millimeter using a plastic graded probe (Hu-Friedy Mfg. Co., LLC, Chicago, IL, USA). The BI will be recorded at two sites per implant (buccal and lingual).

The PLI will be assessed as follows: 0, no plaque in the gingival margin area; 1, a thin layer of plaque on the tooth surface of the gingival margin area, but not visible on inspection if the side of the probe tip is used to scrape the plaque; 2, medium amount of plaque on the adjacent surface; or 3, a large amount of soft dirt in the gingival sulcus or the gingival margin area and the adjacent surface.

The BI will be assessed as follows: 0, no inflammation or bleeding on probing; 1, mild marginal inflammation (slight change in color or texture of any portion, but not the entire marginal or papillary gingival unit) and absence of bleeding on probing; 2, mild marginal inflammation (criteria as above but involving the entire marginal or papillary gingival unit) and slight gingival sulcus bleeding on probing; 3, moderate inflammation (glazing, redness, edema, and/or hypertrophy of the marginal or papillary gingival unit) and linear gingival sulcus bleeding on probing; or 4, severe inflammation (marked redness, edema, and/or hypertrophy of the marginal or papillary gingival unit) and bleeding on probing over the sulcus. When recording bleeding, the probing force will be no more than 15 g.

Two examiners will be trained prior to and during the trial to achieve maximum reproducibility of the measurements [21]. For continuous periodontal clinical parameters (PD), the standard error of the measurement will be evaluated. The average level of agreement between the two examiners will be considered satisfactory when greater than 90% (kappa test) for the other clinical variables.

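### Read literally, an inflamed implant with bone loss above 0 and up to 2 mm is neither mucositis nor peri-implantitis, and the text does not say whether the 2 mm threshold applies throughout

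*Protocol article*

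**What the plan says.** All three implant states are defined in the X-ray assessment section of the protocol article.

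- Peri-implantitis: probing depth (PD) of 5 mm or more, with suppuration or a bleeding index (BI) of 1 or more, "and radiographic evidence of bone loss" of more than 2 mm. An alternative route follows: "or according to consensus [25".
- Mucositis: "Peri-implant mucositis is defined as being positive for suppuration or BI of" 1 or more, "with no radiographic evidence of bone loss. A healthy implant site is defined as a PD of" 4 mm or less. The second half of that quote opens the definition of health.
- Health: PD of 4 mm or less, BI of 0 and, again, no bone loss on the radiograph. Suppuration is not mentioned.

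The same section states that "peri-implant MBL will be measured to the nearest millimeter". The Clinical assessment section describes BI 1 as mild inflammation of part of the margin, "but not the entire marginal or papillary gingival unit) and absence of bleeding on probing".

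Biological complication rates are in the first objective, and mucosal condition is a primary outcome. The two disease incidences are determined at 1, 3 and 5 years and compared by chi-square test (Statistical analysis).

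**The concern.** The bone-loss criterion has a number in one definition and none in the other two. Read as written, the mucositis and peri-implantitis definitions do not meet: between no loss and 2 mm of loss there is a band in which an inflamed implant has no label.

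An inflamed implant that starts to lose bone drops out of the mucositis numerator and does not enter the peri-implantitis numerator. Worsening therefore lowers the recorded complication rate. The band also covers the bone loss that the plan itself expects. If the reading is chosen only when the data are analysed, the same records support two quite different mucositis rates.

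**Working it through.** The plan gives no figure for the share of implants in each state, so there is none to reproduce. The check uses the plan's bone-loss figures and a listing of all combinations of findings.

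**Inputs.** The Sample size section says that at 5 years "peri-implant bone loss in metal-resin/metal-ceramic IFCDPs was" 0.9 mm (SD 0.4), against 0.6 mm (SD 0.1) for ceramic. Recording is to the nearest millimetre (X-ray assessment). Normality is assumed.

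**Step 1: true loss above 0 and up to 2 mm**, Φ((2 − m)/s) − Φ((0 − m)/s).

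- Metal: Φ(2.75) − Φ(−2.25) = 0.9970 − 0.0122 = 0.985. Above 2 mm: 0.003.
- Ceramic: Φ(14) − Φ(−6), about 1. Above 2 mm: about 0.

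**Step 2: loss recorded as 1 or 2 mm**, Φ((2.5 − m)/s) − Φ((0.5 − m)/s).

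- Metal: Φ(4) − Φ(−1) = 0.99997 − 0.1587 = 0.841.
- Ceramic: Φ(19) − Φ(−1) = 1 − 0.1587 = 0.841.

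The remaining 15.9% in each arm would be recorded as 0 mm. Under the literal reading only these could count as mucositis, so the 5-year mucositis rate could not exceed about 16% however much inflammation there was.

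**Step 3: sensitivity.** Gamma and lognormal distributions with the same means and SDs give 98.2% to 98.6% (metal) and about 100% (ceramic) for true loss, and 84% to 88% for recorded loss. If the quoted SDs are between patients and implant SDs are 1.5 to 2 times larger (an assumption), true loss in the band is 79% to 90% (metal) and above 99.8% (ceramic), and recorded loss 67% to 75%.

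**Step 4: effect of the reading on the rate.** Suppose, for illustration only, that inflammation is unrelated to recorded bone loss. The literal reading counts 0.1587 of inflamed implants as mucositis, and the threshold reading almost all of them: a ratio of about 1/0.1587 = 6.3. With SDs twice as large it is about 0.9772/0.3085 = 3.2 in the metal arm.

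**Step 5: all combinations.** Two PD levels × suppuration yes or no × BI 0, 1, or 2 and above × bone loss of 0, above 0 to 2, or above 2 mm give 36 combinations.

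| Reading | In no category | In two categories |
|---|---|---|
| Literal | 20 | 1 |
| 2 mm threshold throughout | 9 | 2 |

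Under the literal reading all 12 combinations with loss above 0 and up to 2 mm are unplaced, 10 of them inflamed. Under the threshold reading the 9 left are:

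- loss above 2 mm with PD of 4 mm or less: 6, of which 5 are inflamed;
- PD of 5 mm or more without inflammation: 3.

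The double placements are suppuration with BI 0, PD of 4 mm or less and no bone loss (under the threshold reading, also loss up to 2 mm). These are both mucositis and healthy.

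**The case against.** The strongest reply is that the 2 mm in parentheses defines the phrase that the next two sentences repeat. That is a natural reading and it closes the main gap. It stands as a possible reading, but nothing in the text fixes it.

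The reply is also right that the stated peri-implantitis rule carries its own threshold, so its numerator is the same under both readings. A reader might infer that both rates are unstable for this reason; only mucositis is. For peri-implantitis the open point is the consensus clause. Its content is not in the document, so whether it conflicts with the stated rule cannot be judged.

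Nor do two rates need an exhaustive classification. An uninflamed implant with a deep pocket is simply a non-case for both, and no healthy rate is tested, so the overlap between mucositis and health does not change either tested rate. What survives is the inflamed implant with loss above 2 mm and PD of 4 mm or less, which counts as neither disease under either reading unless the consensus clause captures it.

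A reader might also infer that taking BI 1 as disease is an error, because "and absence of bleeding on probing; 2, mild marginal inflammation" shows that bleeding is absent at that grade. The documents do not support this. The index grades inflammation and bleeding together, BI 1 is inflammation, and a cut-off of 1 complements BI 0 for health. Table 1 labels the assessment as bleeding on probing, which is a reason to report the stricter cut-off as well, not to replace the sponsor's.

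Finally, PD, X-ray indices, PLI and BI are each compared in their own right, and the sample size rests on bone loss, so much of the trial does not depend on these categories.

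**Conclusion.** The definitions need reconciling. As written, inflamed implants with loss above 0 and up to 2 mm have no stated category, and the mucositis rate falls as they lose bone. The plan's figures put about 98.5% and 100% of true 5-year values in that band, and about 84% per arm of recorded values.

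This rests on normality and on 5-year figures from a cited study, with implant or patient level not stated; the article gives no figures for years 1 and 3. A reader might infer that nearly all implants would go unclassified as inflamed, or that one arm would lose more mucositis cases than the other. Neither follows. No inflammation rate is given, so the share that is both inflamed and unplaced is unknown, and the recorded share in the band is the same 84% in both arms. The supported conclusion is that one set of records yields two mucositis rates, and the text does not choose between them.

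**What to change.** Settle the wording before the 1-year interim analysis.

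1. Use one explicit bone-loss threshold in all three definitions: the plan's own 2 mm, taken as change from the Month 0 radiograph. Inflamed implants with loss of 2 mm or less that do not meet peri-implantitis then count as mucositis.
2. Add absence of suppuration to the definition of health.
3. State how inflamed implants with loss above 2 mm and PD of 4 mm or less are counted.
4. Make either the stated rule or the consensus rule primary for peri-implantitis, and the other a named sensitivity analysis.
5. Leave the PD criterion and the BI cut-off as the sponsor's choice. Because BI 1 means no bleeding, also report mucositis at BI of 2 or more as a sensitivity analysis.

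The cost is endpoint wording and a small added analysis. The Month 0 radiograph, PD, BI and suppuration are already collected.

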### Laboratory assessment

#### Microbiological monitoring

##### Sample collection

Sulcus sampling will be performed immediately before prosthetic treatment and every 6 months after implantation of the final prostheses. Before sampling, antimicrobial mouth wash should not be used within the past 48 h and the patient should not eat within the past 1 h. Prior to sampling, clinical sites will be isolated and dried. Then, any supragingival/supramucosal plaque and calculus will be carefully removed. Submucosal plaque around one single implant will be sampled by inserting 4 sterile paper points (no. 30) into the base of the sulcus or pocket for 20 s. The paper points will be placed in labeled Eppendorf tubes, frozen, and transported to our laboratory for DNA extraction. Four paper points around one single implant will be grouped for analysis.

##### Processing of microbiological samples

Bacterial identification and classification will be determined by sequencing of the V1 and V3 regions of the 16S rRNA gene and amplification by polymerase chain reaction (PCR), as well as library preparations, library quality inspections, and quantifications of DNA samples of the oral flora. The identified TAG sequences will be used for sample differentiation. Qualified libraries will be sequenced with the Hiseq 2500 high-throughput sequencing platform (Illumina, Inc., San Diego, CA, USA). Paired-end reads obtained by Hiseq/Miseq sequencing will be spliced into one sequence and the target sequence subjected to quality control filtering. The filtered sequence will be compared with a reference database, and the chimeric sequence will be removed to obtain the final optimized sequence. Operational taxonomic unit (OTU) cluster analysis and species classification annotations are based on optimized sequences, diversity index analysis is based on OTU clustering results, and species structure and difference analyses are based on taxonomic information. Beta diversity analysis, principal co-ordinate analysis (PCoA), and linear discriminant analysis (LDA) effect size analysis will be used to compare differences in microbial diversity and in significant microbial species between the two treatment groups.

#### Surface roughness assessment

The tests will be performed before prosthetic delivery and every 6 months after implantation of the final prostheses. For standardization, surface roughness measurements will be made at six points around each abutment (mesial buccal, buccal, distal buccal, distal lingual, lingual, and mesial lingual). For each point, measurements and analysis will be repeated twice. The reproducibility will be assessed by calculating the intraclass correlation coefficient with a confidence interval of 95%.

### Randomization, allocation, and blinding

The subjects will be randomly allocated to one of two groups according to the prosthetic materials: titanium framework with acrylic resin veneering (group 1) or zirconia framework with/without ceramic veneering (group 2). The allocation of patients will be randomized using computer-generated permuted block randomization with an allocation ratio of 1:1. Randomization will be performed by sealed envelopes that will be opened after final impressions are obtained.

Microbiota analysis will be blinded after assignment to the intervention groups. Each sample will have a number associated with an allocation sequence, as well as information pertaining to the dental position and acquisition time. The technician conducting the PCR analysis will be blinded to the source of the sample. Interim statistical analysis will be performed at 1 and 3 years after implantation of the final prostheses. Final statistical analysis will be conducted at the end of the trial with the analyst blinded to both patient allocation and the interim analysis results.

